#### Organizational setting factors

To assess staff levels and qualifications, we ask supervisors about workforce characteristics (*e.g*., the number of licensed and certified staff, and staff to client ratio) using questions from a survey of adolescent treatment providers [53]. This information will help us determine whether program composition affects A-CRA sustainment. Supervisors are asked about the annual turnover rates for administrative and clinical staff. We also will use turnover information from the implementation period from archival sources. We ask clinical staff about their perceptions of leadership support in the interview. In addition, we included a recently published scale in the online survey designed to assess leadership support of EBT implementation [54].

#### Organizational climate

We use items from the Organizational Readiness for Change (ORC; [35]), which asks about motivation for change, resources, staff attributes, and organizational climate. ORC data was also collected from staff at each of the CSAT-funded organizations during the funding period.

#### Organizational type and capacities

As part of the survey, supervisors are asked questions about the composition of the organization (*e.g*., type of agency [*i.e*., substance abuse treatment services, mental health services, general health care, other], types of payment accepted [*e.g*., Medicaid, SCHIP, private health insurance], other funding sources [federal, state, local government and/or foundations], and clients [age ranges]). These organizational questions are similar to those asked either by National Survey of Substance Abuse Treatment Services [44] and Knudsen [53], a survey specifically designed for adolescent treatment providers. Also, a recent measure developed to assess program sustainability capacity (Washington University, 2012 [55]) is included.

#### Intervention characteristics

##### Perceptions of the A-CRA intervention

We assess A-CRA perceptions in a number of ways. In the interviews, we ask an open-ended question about what respondents thought about A-CRA, which will then be coded for analyses. As part of the survey*,* modified items from O’Loughlin *et al*. [26] are used to assess perceived compatibility, difficulty and effectiveness. Following Rogers’ theory of innovation diffusion, we also employ Steckler *et al*.’s [56] relative advantage and complexity scales, shown to have high reliability (alphas = 0.88 and 0.83, respectively).

##### Attitudes toward A-CRA intervention

We modified survey items developed by Lin *et al*. [57] that assess expectancies, instrumentality and valence associated with implementing a new initiative. These scales have been shown to be related to organizational commitment to implementing new healthcare initiatives.

##### Plans for sustainment and spread

Feinberg *et al*. [58] found that planning for sustainment was predictive of coalition sustainment. We ask supervisors about their organization’s plans to sustain A-CRA.

##### A-CRA facilitators and barriers

We use items developed by Scheirer *et al*. [17] to ask all supervisors and clinicians about the factors that facilitated and impeded A-CRA delivery regardless of whether they report sustainment or not. If staff report that they are no longer delivering A-CRA, we ask about the reasons for stopping it (*e.g*., ‘When did you stop delivering A-CRA?’, ‘What were the main reason(s) that you stopped delivering it?’) and ask those that report sustainment the reasons that helped them maintain it (*e.g*., ‘What has helped you maintain A-CRA since the loss of CSAT funding?’). We use these data to meet the first study aim.

### Analytic plan

This study involves the use of both qualitative and quantitative analytic methods. The first aim of describing sustainment and the associated innovations, facilitators and barriers will be addressed primarily with qualitative methods. We employ multiple strategies to avoid bias in the analysis and interpretation of the qualitative data by including the use of a multidisciplinary team (rather than a single observer) to collect and analyze the data. In addition, standardized instruments along with semi-structured interview protocols are used to decrease the possibility of bias.

Raw data will be cleaned and descriptive statistics will be conducted at first to check the data quality and integrity for every variable in the raw data. In case of missing information on the quantitative measures, multiple imputation and nonresponse weights will be implemented [59]. All data will be aggregated to the program by time level for subsequent analyses. We recognize that our study design includes data from different time points based on when the organization lost or will lose funding and our proposed data collection period (2013 to 2015). The mixed model can handle these unsynchronized longitudinal measurements so that we can consistently estimate the association between the predictors and the proposed outcomes.

Next, preliminary exploratory analyses will estimate the unadjusted mean trajectories of sustainment outcomes over time among all sites as well as for each site by growth curve models [60] to address the goals of the first study aim. A cluster analysis will [61] identify potential groups of sites where sites in a group will have relatively similar trajectories. If such groups exist, descriptive statistics will be conducted to summarize and compare the mean characteristics of all groups.

In order to address the second study aim, hierarchical mixed-effect models will be applied to estimate the effects of predictors on the sustainment outcomes. These models will include the fixed effects for all study factors and covariates as well as the random effects for site-level temporal trends. Cohorts of sites will also be controlled to account for differences among funding waves. Fixed effects consist of both static factors, *e.g*., implementation quality during funding period, and time varying factors, *e.g*., external funding support. Correlation analyses among predictors and the variance inflation factors will be used to evaluate the potential multicollinearity in fixed effects. If necessary, a model selection procedure such as backward-elimination regression will be applied to drop some correlated predictors. Statistical significance of a predictor will be tested by Wald’s test (z-test) or the likelihood ratio test (chi-squared test) after fitting the final mixed-effect models. F-tests will also be conducted to test multiple factors simultaneously, *e.g*., external supports received during the implementation period (static) and after the implementation period (time-varying).

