### Study aims and hypotheses

The first study aim is to characterize levels of A-CRA implementation longitudinally for 84 programs that received federal funding to implement A-CRA. In doing so, we will identify which aspects of A-CRA are sustained, innovations in its implementation, and potential facilitators and barriers to implementation. We will also characterize the trajectory of implementation quality among the 84 programs over time. We hypothesize that substantial changes in implementation quality will occur after funding ends. Specifically, we expect to observe an overall decrease in sustainment over time.

The second study aim is to empirically evaluate factors that predict the degree to which programs sustain A-CRA. We hypothesize that the extent to which A-CRA is sustained will be associated with community/outer context (*e.g*., reimbursement for services), organizational/inner context factors (*e.g*., presence of trained supervisors at the end of the funding phase), and intervention-specific characteristics (*e.g*., staff support for A-CRA).

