### Data sources

#### Overview

We will rely on two sources of data: a) secondary data on implementation quality and organizational functioning that were collected during the funding period; and b) primary data collected at three time points during the study to measure the extent of sustainment and a number of hypothesized predictor and control variables.

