#### Primary data

For this project, we will collect data over three regularly scheduled intervals (approximately every nine months) to assess the level of sustainment (*i.e*., our main dependent measure) and hypothesized predictor and control variables. The first data collection occurred within one year of project funding (*i.e.,* Fall 2013). For the majority of the sites (*i.e*., the AAFT4 2010 cohort, n = 34), the primary data will include data from the last quarter of funding and two times following that period (*i.e*., at time of loss of funding, and approximately one and two years later). For the oldest cohort funded in 2006, the project will collect data approximately 48 months post-funding and up to 72 months post-funding.

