### Data collection procedures

#### Primary data collection

Primary data collection will consist of telephone interviews, online surveys, and audiotaped treatment sessions from key staff (*i.e*., clinical supervisors and clinicians). Staff from each of the treatment sites that were responsible for A-CRA delivery (or outpatient adolescent treatment in general, if it is reported that A-CRA is no longer being delivered) are being recruited. During the funding period, most programs had two clinicians trained. We used this estimate to budget for data collection and analyses.

All data collection is voluntary and confidential. Our strategy is to use multiple methods (*i.e*., mail, phone, and email) to introduce and remind the participants about the data collection opportunities, consistent with effective tailored survey methods [49]. Prior to the data collection, we explain the purposes of the research through both an email and by phone and then ask for participation in the study. If we are not able to contact by email or phone, the information and request is sent by mail (using FedEx).

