#### Surveys

After the semi-structured telephone interview, we ask respondents to complete an online survey to ascertain characteristics of the facility in which the treatment was delivered that will serve as covariates in our analyses (*i.e*., program-specific factors) and other standardized scale measures of organizational or clinical support (see Table 2 for a list of measures). Our experience with data collection suggests that higher survey response rates will be achieved if it is conducted following the interviews, and this is also consistent with recent data collection approaches in this field [51].

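### Time-varying predictors are collected in the same waves as sustainment, so the Aim 2 model, read as concurrent, supports associations and not effects for those factors

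*Protocol article*

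**What the plan says.** The second aim is to "empirically evaluate factors that predict the degree to which programs sustain A-CRA" (Study aims and hypotheses). The Data sources overview describes "primary data collected at three time points during the study to measure the extent of sustainment and a number of hypothesized predictor and control variables", and the Primary data section spaces the three waves about nine months apart. Outcome and time-varying predictors therefore share a wave.

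The informants are clinical supervisors and clinicians. Staff remain eligible after a site has stopped: those responsible for "outpatient adolescent treatment in general, if it is reported that A-CRA is no longer being delivered" are also recruited (Primary data collection). Within a wave, "After the semi-structured telephone interview, we ask respondents to complete an online survey" (Surveys), and recordings for fidelity rating are also requested after the interview. Table 2 assigns managerial support and champions to clinicians, perceptions of A-CRA to clinicians, attitudes to both roles, and external support and referrals to supervisors.

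The Analytic plan aggregates everything to one record per program and time point. It then states that "hierarchical mixed-effect models will be applied to estimate the effects of predictors on the sustainment outcomes", with fixed effects for static and time-varying factors, random site-level time trends and control for cohort. It mentions no lag, no ordering in time and no separation of between-site from within-site variation. The Limitations section does not mention reverse direction.

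**The concern.** A site that has given up A-CRA may report no champion, weaker managerial support and a poorer view of the treatment because it gave A-CRA up. When the outcome and these answers come from the same wave, a same-wave coefficient mixes that path with the one that Aim 2 is after. Random site trends and cohort terms do not remove it, because the link arises within the wave. One coefficient per time-varying factor also merges two different comparisons: sites that differ on average, and the same site changing over time.

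Two further features of the plan could carry the problem into the reported results. The joint F-test that combines external support during and after funding could be significant because of the later part alone. Backward elimination among correlated predictors could keep a same-wave factor and drop an earlier static one.

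The Discussion promises recommendations for policy and clinical practice. Factors that merely follow discontinuation could be presented there as means of preventing it.

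**Working it through.** **1. The plan's own figures.** Inputs from Estimated sample size and statistical power: 64 programs, 3 time points, ICC 0.1. Alpha and power are not stated; two-sided 0.05 and 80% are assumed.

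- Dichotomous predictor, equal split: design effect 1 + (3 − 1) × 0.1 = 1.2; effective n = 192 / 1.2 = 160; MDE = (1.960 + 0.842) × √(4/160) = 0.443 SD, against 0.45 stated.
- Continuous predictor, n = 64: tanh(2.802 / √61) = 0.344, against 0.34 stated.

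Both reproduce.

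**2. A predictor with no effect, but with answers that respond to sustainment.** Let sustainment y have ICC 0.1 and let the answer at the same wave be x = g·y + √(1 − g²)·noise. The protocol gives no value for g, so a range is shown. The same-wave model is a random-intercept mixed model with wave terms. The lagged model regresses y at wave t on x and y at wave t − 1, with cluster-robust errors. There were 200 runs per row.

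| g (assumed) | Same-wave slope | Same-wave significant | Lagged, prior-adjusted significant |
|---|---|---|---|
| 0 | 0.00 | 5% | 6% |
| 0.1 | 0.09 | 22% | 4.5% |
| 0.2 | 0.20 | 81% | 9% |
| 0.3 | 0.29 | 99% | 6.5% |
| 0.4 | 0.39 | 100% | 7.5% |

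A separate run gave 28%, 83% and 99% for g = 0.1, 0.2 and 0.3.

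A hand check agrees. The ICC of x is only g² × 0.1, so the 192 records count almost in full. With g = 0.1, z = atanh(0.1) × √189 = 1.38, and the chance of exceeding 1.96 is about 28%. With g = 0.3, z = 4.26 and the chance is about 99%. A reverse correlation just below the 0.34 that the study is sized to detect would thus nearly always be flagged.

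**3. What a lagged model costs.** Two intervals per site remain: effective n = 128 / (1 + 0.1) = 116.4; MDE = 2.802 × √(4/116.4) = 0.519 SD, against 0.443.

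**4. What a lagged model can miss.** Suppose instead that x has a genuine same-period effect on y with correlation g and there is no reverse path. Standardize both, with ICCs ρx and ρy. Then corr(y at t, x at t − 1) = g·ρx, corr(y at t, y at t − 1) = ρy and corr(x, y in one wave) = g. The lagged coefficient of x, adjusted for prior y, is (g·ρx − g·ρy) / (1 − g²). It is zero when ρx = ρy, and has the wrong sign when the predictor is less persistent than the outcome. In simulation with g = 0.3 and both ICCs at 0.1 or 0.5, the lagged model was significant in 5–7% of runs and the same-wave model in 93–99%.

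**The case against.** The case against has several parts that stand.

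- **The measures are not all from one interview.** A reader might infer that they are. Predictors come from interview, survey and archives, and respondents differ by construct in Table 2. The fidelity part of the outcome is rated by an expert from recordings requested after the interview. Same wave, and largely the same pool of staff, is as far as the document goes.
- **Part of Aim 2 is properly ordered.** Clients served, certification, sessions and 12-month recovery come from the funding period and enter as static factors. So can readiness for change: "ORC data was also collected from staff at each of the CSAT-funded organizations during the funding period". None of these is affected.
- **The language is partly associational already.** The Aim 2 hypothesis is framed as association, and so is the Analytic plan's remark on unsynchronized measurements. The design is openly observational.
- **The only time-varying example in the Analytic plan is external funding support**, which is less open to reverse influence than opinions of A-CRA. That staff perceptions enter as time-varying factors is an inference from Table 2 and the three-wave collection.
- **An article may leave lag structure to a fuller analysis plan.** Its absence is not a fault in itself, and a lagged specification is not excluded.

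What remains is that the article does state the model, the data that feed it and the claim to estimate effects. For factors measured with the outcome, a model read as concurrent does not support that claim.

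A reader might also infer that the lagged, prior-adjusted model should become the primary one. Step 4 of the working argues against this: that model can erase or reverse a genuine same-period effect. Its low false-positive rate also depends on a well-measured outcome. With outcome reliability 0.6, ICC 0.5 and reverse correlation 0.5, one simulation gave 21% false positives.

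**Conclusion.** The point holds for time-varying predictors measured in the same wave as sustainment, most clearly perceptions of and attitudes to A-CRA, managerial support and champions. For these, a claim to estimate effects is stronger than the described design supports. Static funding-period predictors are not touched.

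The size is conditional. At an assumed reverse correlation of 0.1, about 22–28% of same-wave tests of a null predictor are significant; at 0.2, 81–83%; at 0.3, 99%; with no reverse influence, 5%. These figures assume 64 sites, 3 waves, ICC 0.1 and a two-sided 5% test. Nothing in the protocol shows which value applies, so the estimates can include reverse influence; it does not follow that they will. The power figures in the protocol are not in question here.

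**What to change.** 1. Report same-wave coefficients of time-varying factors as associations, in line with the Aim 2 hypothesis, and add reverse direction to the Limitations.
2. Split each time-varying factor into its site mean and the deviation from that mean, and report both coefficients.
3. Report associations with expert-rated fidelity separately from those with the organizational elements reported by staff.
4. Add, as a sensitivity analysis and not as the primary model, sustainment at wave t on predictors at wave t − 1, adjusted for prior sustainment. For the first wave, use funding-period readiness-for-change data and archival turnover.

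No new data are needed. The cost is more coefficients and more analyses to report. The lagged model is less precise (MDE about 0.52 instead of 0.44 SD, under two-sided 0.05, 80% power and an equal split), and predictors without a funding-period value have two outcome waves instead of three. The first-wave lag would also differ by cohort, since the 2006 cohort is first seen about 48 months after funding, and funding-period implementation measures would have to stand in for a prior sustainment score. Because the lagged model can miss genuine same-period effects, the plan should say that a null lagged result is not evidence of no effect.

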The level of implementation refers to how well an EBT was delivered during the funding period. In this study, we assess level of implementation in reference to employing clinical and supervisory staff who have demonstrated competency through the certification processes and an organization having recruited and treated a sufficient number of participants during the initial implementation period, also termed as ‘penetration’ [32,33]. Integral to Rogers’ [20] innovation diffusion theory is that the implementation experience will have a large influence on sustainment. Poor implementation may lead to ‘discontinuance’ (*i.e*., rejection) of an innovation. We have available participant process (*e.g*., treatment initiation, engagement, satisfaction) and outcome data to help explicate implementation during the funding period. Opinions are mixed as to whether these data will help predict level of sustainment [34]. Intuitively, it is sensible to expect that the extent to which clinicians are able to engage participants in an intervention or participants are able to achieve a treatment’s objectives would be related to sustainment. However, such factors as external (*i.e*., community) or internal (*i.e*., organizational) support may trump any efforts to sustain an effective EBT. Therefore, we examine these issues in our study.

Factors within the organizational setting refers to characteristics of the ‘inner context’ [29], such as institutional (*e.g*., leadership support, resources within the organization for EBT delivery), organizational climate [35], and staff attributes (*e.g*., presence of a program champion, motivation and skills to deliver the EBT). Although studies have shown that staff turnover is not predictive of sustainment [17], we believe that with a complex treatment like A-CRA, attrition of trained staff will impede sustainment. Intervention characteristics, such as community-based providers’ perceptions of the treatment, may influence whether it is sustained [20]. It is not known whether program leadership will still be in support of the treatment at the end of the grant period and whether staff will be motivated and trained to deliver it, so we plan to assess these factors in this study.

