### Relationships among variables

It is important to acknowledge that the four factors described above do not operate in isolation from one another [22]. Researchers have emphasized the dynamic context of the community in fostering sustainment, whereas both Gruen *et al*.’s [25] and Shortell’s [22] work emphasized the interaction between components (*e.g*., tailoring a treatment to organizations and the community context) and over time (*e.g*., integrating the treatment within existing structures). To better address this point, we will assess these factors through multiple methods across time, including qualitative semi-structured interviews and standardized survey questions that will help us better ascertain the association among these factors. For example, we will ask staff about how the treatment was or was not integrated into their existing organization and whether adaptations were made to the treatment to make it feasible to continue its delivery without the support provided during the funding period.

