#### Secondary data

Extensive data was collected during the funding period on implementation quality and organizational functioning. Records of the number of clinicians and supervisors trained and certified at each funded program, and the number of sessions and A-CRA procedures delivered to each client were recorded. Data from clinical staff on organizational functioning was also collected. In addition, the number of adolescents that were treated at each funded program, the number of treatment sessions each client received, and the treatment length of stay was recorded. The client-level outcome dataset that contains baseline, 3-, 6-, and 12-month follow-up data on substance use and functioning is available from clients who receive A-CRA at the funded sites. No individual-level identifiers are included in the secondary dataset. This dataset will be useful to help characterize implementation quality during the funding period and serve as predictor variables to test our hypothesis as to whether programs that were able to successfully implement A-CRA during the funding period are more likely to sustain it than programs that were not successful at implementation during the funding period.

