#### Community environment factors

Supervisors are asked about local, state and federal support (external support) since the end of federal funding. In these contexts, community participation typically encompasses the provision of referrals to receive care. We ask supervisors about the main sources of A-CRA referral and of their treatment program overall. We ask this in both the interview and survey to capture: a) descriptive information about the reasons for the different referral sources and document any changes over time to help address community need, and b) systematically collect comparable information across the programs on their main sources of referral. We also ask questions related to dissemination efforts and community involvement in the treatment to capture efforts made by the organization to build community support for their program [17]. Supervisors will be asked about the introduction and continuation of other adolescent SUD treatment providers in their area to assess community need changes.

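### The hypothesis that good funding-period implementation leads to sustainment is tested only conditionally on later factors that it may itself have shaped, so the tested coefficient can understate the overall relation

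*Protocol article*

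**What the plan says.** The Analytic plan section fixes the content of the second-aim models: "These models will include the fixed effects for all study factors and covariates as well as the random effects for site-level temporal trends". It gives examples of the two kinds of fixed effect that enter together: "implementation quality during funding period, and time varying factors", the latter illustrated by external funding support. Each predictor is tested by a Wald or likelihood ratio test once the final model has been fitted. Multicollinearity is checked, backward elimination may be used, and F-tests of several factors together are planned. The article describes no model that holds funding-period factors without the later ones.

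The hypothesis on funding-period implementation is in the Secondary data section: "programs that were able to successfully implement A-CRA during the funding period are more likely to sustain it than programs that were not successful". The Background gives its rationale, that integral to "innovation diffusion theory is that the implementation experience will have a large influence on sustainment".

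On timing, the Overview of data sources describes "primary data collected at three time points during the study to measure the extent of sustainment and a number of hypothesized predictor and control variables". One such predictor is described under Community environment factors: "Supervisors are asked about local, state and federal support (external support) since the end of federal funding". Leadership support, perceptions of and attitudes toward A-CRA, and plans to sustain it are likewise collected at the study waves. The section on relationships among variables says that "the four factors described above do not operate in isolation from one another".

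**The concern.** The hypothesis asks whether programs that implemented well went on to sustain more. That is most naturally read as an overall association. The planned coefficient asks a narrower question: among programs with the same later external support, leadership support, staff views and plans, did those that implemented better during funding sustain more?

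The two questions have the same answer only if the later factors are not consequences of funding-period implementation. Some plausibly are. Staff views on how effective or difficult A-CRA is would be formed largely by delivering it, and plans to continue would follow from that experience. To the extent that this is so, holding those factors fixed removes part of the relation under test.

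A stated hypothesis could then be reported as unsupported because of how the model was built. The predictors affected are those measured before the outcome, and those a funder can still influence while a grant is running.

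**Working it through.** **Inputs from the article** (sample size section): 64 programs, 3 time points, intra-class correlation 0.1, detectable difference about 0.45 SD, detectable correlation about 0.34, from a simplified bivariate calculation. **Assumed, because not stated:** two-sided alpha 0.05 and 80% power, so z-sum = 1.960 + 0.842 = 2.802.

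**1. The plan's own figures.**
- Dichotomous predictor: effective n = 192/(1 + 2 × 0.1) = 160. Detectable difference = 2.802 × √(4/160) = 0.443 SD, against 0.45 stated.
- Continuous predictor: r = tanh(2.802/√(64 − 3)) = 0.344, against 0.34 stated.

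Both reproduce. The second uses n = 64 and so ignores the repeated waves. Results are therefore shown below both at n = 64 and for the 64 × 3 layout.

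**2. Power for the overall association.** With r = 0.34 and n = 64: Φ(atanh(0.34) × √61 − 1.960) = 79%.

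**3. Joint model.** Let X be a funding-period factor, M one later factor and Y sustainment, all standardised. Assume a total effect of 0.34, corr(X, M) = a, and a share m of the total effect running through M. The article gives neither a nor m. Then:
- coefficient of X given M: c = 0.34 × (1 − m)
- coefficient of M: b = 0.34 × m/a
- R² = c² + b² + 2abc
- partial correlation of X: c√(1 − a²) / √(1 − R² + c²(1 − a²))
- power from the Fisher z test of that partial correlation, with √(64 − 4).

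Worked case, a = 0.5 and m = 0.5: c = 0.17, b = 0.34, R² = 0.0289 + 0.1156 + 0.0578 = 0.2023. Partial r = 0.1472/√0.8194 = 0.163, and power is 25%.

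**4. Range over m, with a = 0.5.** The last two columns come from a simulation of 64 programs × 3 waves, residual intra-class correlation 0.1, 1,000 runs, analysed on program means, with M constant over waves.

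| Share mediated | Coefficient of X given M | Partial r | Power, n = 64 | Rejection, 64 × 3, with M | Rejection, 64 × 3, without M |
|---|---|---|---|---|---|
| 0% | 0.34 | 0.299 | 67% | 96% | 98% |
| 25% | 0.255 | 0.231 | 45% | 84% | 99% |
| 50% | 0.17 | 0.163 | 25% | 53% | 98% |
| 75% | 0.085 | 0.088 | 11% | 21% | 96% |
| 100% | 0 | 0 | 5% | 4% | 95% |

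The simulated model without M returned a coefficient of about 0.34 in every row.

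**5. Sensitivity to a.** At half mediation and n = 64, power is 37% for a = 0.3 and 17% for a = 0.7.

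**6. Separating two causes.** With no mediation, power at n = 64 already falls from 79% to 67% because X and M are correlated. That part is the ordinary cost of correlated predictors and involves no change in the coefficient. The further fall, from 67% to 25% at half mediation, goes with the smaller coefficient.

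**The case against.** The strongest reply is that the joint model answers a question the authors do pose. The Background suggests that external or internal support may outweigh other influences on whether an effective treatment is kept, and says the study will examine this. Both sets of factors must be in one model for that. The formal second aim speaks of prediction and association, and the hypothesis does not say whether it is adjusted or unadjusted. This stands, and it is why the joint model should be kept. It does not supply a test of the overall relation.

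Second, the article draws no mediation path. It says only that the factor groups are interdependent. This stands too: mediation is an inference here. Not every later-surveyed variable is a consequence of implementation. Agency type and age of program are more plausibly confounders, and adjusting for them is proper. Readiness and turnover data also exist from the funding period. For the 2010 cohort (n = 34), the first wave covers the last quarter of funding, so not all wave data are post-funding.

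Third, the joint F-tests and backward elimination might be thought to help. The F-test example pools external supports during and after funding and does not isolate funding-period implementation. Backward elimination could drop either the earlier or the later factor, which leaves the data to decide which question is answered.

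Fourth, a condensed article may leave model sequence to a fuller plan. That is fair, and nothing in the text excludes an additional model. The point rests on the model the article does specify.

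A reader might infer that the funding-period effect is wholly adjusted away. That needs full mediation, which nothing in the document establishes. A reader might also infer that a helpful factor would appear harmful. This needs a strong unmeasured cause of both the later factor and sustainment. For example, take X→M = 0.5, M→Y = 0.3, no direct effect, and unmeasured paths of 0.5 to both M and Y. The true total of 0.5 × 0.3 = +0.15 then becomes −0.5 × (0.5 × 0.5/0.75) = −0.17. Every one of those values is an assumption, so sign reversal is a possibility and not a finding.

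**Conclusion.** The point holds as a mismatch between a stated hypothesis and the coefficient specified to test it. The coefficient is conditional on later factors and understates the overall relation in proportion to whatever share runs through them: a half at 50% mediation, all of it at 100%, nothing at 0%. The n = 64 powers match the basis on which the article's 0.34 can be reproduced. The 64 × 3 rejection rates are closer to the planned analysis and less severe, at 53% against 25% for half mediation. Both rest on an assumed total correlation of 0.34, a correlation of 0.5 and a single later factor.

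The article expects better power from the mixed model than from its bivariate calculation. That expectation need not carry over to this conditional coefficient.

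This should be fixed but is not critical: mediation is plausible and unproven, the study is observational, and the joint model has a legitimate purpose of its own.

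**What to change.** Specify the second-aim analysis in time order.

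- **Model 1:** funding-period implementation factors, cohort, and program characteristics that predate or belong to the funding period (for example agency type, age of program, and funding-period readiness and turnover data). Name this as the test of the hypothesis in the Secondary data section.
- **Model 2:** the joint model as now written. Use it to test the later factors, to ask whether contextual support outweighs funding-period performance, and to describe how far the Model 1 associations shrink.
- **Interpretation:** state that funding-period coefficients in Model 2 are conditional on later factors and are not total associations. A null result there should not be reported as evidence against the hypothesis.

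The cost is one more model to fit and report, a rule for which characteristics count as pre-existing, and a few sentences of plan wording. No new data are needed, and only the first wave had been completed when the article was submitted.
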